**Objective 4: Evaluation of the impact of the survey’s modality.**

We will conduct one *microtrial* in order to assess the effect of the survey’s modality (IVR versus CATI) on key survey metrics as described above and to assess inter-modal reliability. A group of participants will receive an IVR survey first, followed by a CATI survey 7 days later. A second group of participants will receive a CATI survey first followed by an IVR survey 7 days later. Whether a participant receives IVR or CATI first will be determined at random, blocking to ensure balance between IVR and CATI participation.

*B.* ***Provide a sample size and a justification as to how you arrived at that number. If you use screening procedures to arrive at a final sample a table may be helpful.***

A description of sample size calculations is provided below in the text and is accompanied with a table.

Baseline Survey: We selected 100 participants with complete surveys as a sample size because we think this a sufficient size sample to ascertain that the survey, incentive, and text message delivery mechanisms are well functioning. Adjusting our sample size to account for a baseline completion percentage of 30% (estimate provided by VOTOmobile), we anticipate to consent and enroll 334 participants per country; 1336 participants in four countries.

Microtrial 1-6:

Sample size calculations will be updated with country-specific completion percentages obtained from the baseline survey.

Assuming a baseline survey completion percentage of 30%, in order to detect an absolute 10% difference in survey completion between two study arms at an alpha of 0.05 and power of 80%, it is calculated that 376 individuals who have completed an IVR survey will be needed in each study arm for each microtrial. With a completion percentage of 30%, we calculated that 1254 participants will be required to consent to the survey per study arm. With 16 study arms in these 6 micro trials, 20,064 participants will be enrolled per country; 80,256 participants in four countries.

Microtrial 7:

This sample size is calculated based on the kappa statistic. With assumption of kappa= 0.75, a margin of error of 0.05%, an alpha of 0.05, and the proportion of positive responses=0.3, 405 participants who have completed the survey per study arm are needed. Adjusting for a 20% loss to follow-up from the first and second mobile phone survey and a 30% baseline completion percentage, 1688 participants who consented will be enrolled per arm and per country, for a total of 3376 participants across the two arms per country. With two arms and 4 countries, a total of 13,504 participants who provide consent across the four studies are needed.

Total Sample Size

For the baseline survey and seven microtrials, in each country, a total of 23,773 individuals who have consented to an MPS survey will be needed to fulfill a sample size of 6926 individuals who completed an MPS survey per country. As this protocol is being implemented in four countries, the overall sample size is 95,092 individuals who have consented to an MPS survey and 27,704 who completed a MPS survey

**Table 1.** Number of participants who consent to and complete a mobile phone survey per country

|  | **Col. A** | **Col. B** | **Col. C^*^**  [(Col B*100)/0.30] | **Col. D**  [Col A*Col B] | **Col. E**  [Col A*Col C] |
| --- | --- | --- | --- | --- | --- |
|  | # of study arms | N participants who completed survey per study arm | N participants who consented per study arm | Total N participants who completed survey | Total N participants who consented |
| **Objective 1** |  |  |  |  |  |
| *Baseline* | 1 | 100 | 334 | 100 | 334 |
| *Microtrial #1* | 3 | 376 | 1254 | 1128 | 3762 |
| *Microtrial #2* | 3 | 376 | 1254 | 1128 | 3762 |
| *Microtrial #3*** | 3 | 376 | 1254 | 1128 | 3762 |
| **Objective 2** |  |  |  |  |  |
| *Microtrial #4* | 4 | 376 | 1254 | 1504 | 5016 |
| *Microtrial #5* | 2 | 376 | 1254 | 752 | 2508 |
| **Objective 3** |  |  |  |  |  |
| *Microtrial #6* | 1 | 376 | 1254 | 376 | 1254 |
| **Objective 4** |  |  |  |  |  |
| *Microtrial #7* | 2 | 405 | 1688 | 810 | 3376 |
| **Total** |  |  |  | 6926 | 23,773 |

* For microtrial 7, we adjust for a 20% loss to follow-up from the first and second mobile phone survey.

In order to better understand reasons for refusal and survey attrition, to assess the usability of the IVR platform and receive feedback on the incentives and survey introductions, we will call a sub-sample of participants from *microtrials #1-5 and #7* and administer a short survey over the mobile phone. For each of these seven *microtrials*, we will call back a random sample of 30 individuals who did not complete the survey, 30 individuals who refused to consent to the survey, and 30 individuals who were identified as non-responders (i.e. did not initiate the survey); representing a total of 540 individuals in *microtrials* *#1-5, and 6,* per country.

**Fig 1**.Survey outcomes and number of participants who will complete a follow-up phone call

**
[figure not shown]
**

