**III. Study Design**

A. ***Provide an overview of your study design and methods. The study design must relate to your stated aims/objectives. Details will be requested later.***

The following objectives will be conducted in four of the following six countries: Uganda, Bangladesh, Tanzania, Kenya, Lebanon, and Ghana. The Bloomberg Philanthropies Data for Health Initiative (under which this work falls), has secured high level government agreements for Tanzania, Bangladesh, and Ghana to date. The four objectives detail a series of seven microtrials. Microtrials will be rapidly deployed, randomized survey deployments of limited sample sizes, sufficient to detect a consequential difference, as described below in Table 2 and will be sent through random digit dialing (RDD). RDD uses the mobile network operator identifying digit sequence as the base (e.g.all of MNO X’s phone numbers start with either 072, 077, or 079) and randomly generates the remaining digits to create a mobile phone number. A built-in randomization schema will randomly fork each dialed participant to one of the arms of the microtrial. To achieve these objectives, JHSPH will partner with in-country research institutes and government bodies. The countries will lead the research activities with support from JHSPH. JHSPH investigators will have no contact with research participants. VOTOmobile, a company that specializes in delivering IVR surveys globally, will be contracted to deliver the mobile phone surveys. De-identified data will be jointly shared with JHSPH and in-country partner investigators.

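### Microtrials 1-6: 376 per arm is the number of respondents whose completion is observed, not the number of completers, so dividing it by 0.30 to reach 1,254 uses the 30% twice

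*Protocol*

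**What the plan says.** Protocol section III.B, under Microtrial 1-6, takes 30% as the baseline completion, with a significance level of 0.05 and 80% power. The size is chosen "in order to detect an absolute 10% difference in survey completion between two study arms". From these inputs the protocol concludes that "it is calculated that 376 individuals who have completed an IVR survey will be needed in each study arm for each microtrial". The next step is "With a completion percentage of 30%, we calculated that 1254 participants will be required to consent to the survey per study arm". Over 16 arms this becomes 20,064 enrolled per country and 80,256 in four countries.

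Table 1 carries the same reading: 376 stands in Column B (completed, per arm) and 1,254 in Column C (consented, per arm). Table 2 also gives the size of microtrials 1-6 as 376 complete surveys per arm. The Total Sample Size paragraph says that "a total of 23,773 individuals who have consented to an MPS survey will be needed" per country, and 95,092 overall.

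The data analysis plan (section V.C, item 4) defines the completion rate as CI/(CI+PI+R): complete interviews over complete interviews, partial interviews and refusals. Refusals include people who did not consent and people who formally withdrew during the survey.

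**The concern.** A sample size for comparing two completion proportions counts the people in the denominator of each proportion. If all 376 had completed, completion could not vary among them and there would be nothing to test. Calling the 376 completers and inflating by 1/0.30 therefore applies the completion percentage a second time.

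This calculation is the only quantitative justification for 80,256 of the roughly 95,000 planned participants, all of whom are approached by unsolicited calls or messages. It also misdescribes what the trial will detect. Differences well below the 10 points named as the target will reach significance, and the incentive carried forward from microtrial 1 depends on whether there is an appreciable difference between arms.

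A second, linked problem is the denominator. The sample size section applies the 30% to people who consented, whereas the analysed rate also counts refusals.

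**Working it through.** **Inputs** (section III.B): p1 = 0.30; p2 = 0.40; alpha 0.05; power 0.80. The protocol states neither sidedness nor direction. Two-sided and upward are taken because only they reproduce 376. Equal arms are assumed from the equal N per arm.

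**Step 1: reproduce 376.** Without continuity correction:

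n = [1.960·√(2·0.35·0.65) + 0.8416·√(0.30·0.70 + 0.40·0.60)]² / 0.10² = (1.3221 + 0.5646)² / 0.01 = 355.9

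With continuity correction:

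n′ = (n/4)·[1 + √(1 + 4/(n·0.10))]² = (355.9/4)·(1 + 1.0547)² = 375.7, rounded up to **376**, the protocol's figure.

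Other variants do not give 376: unpooled 354; arcsine 356; one-sided 281 (300 corrected); 30% versus 20% two-sided 294 (313 corrected).

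So 376 is the number per arm with observed completion status. It would contain about 0.30 × 376 = 113 completers in one arm and 0.40 × 376 = 150 in the other.

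**Step 2: the second use of 30%.** 376/0.30 = 1,253.3, rounded up to 1,254. Ratio 1,254/376 = 3.34.

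- Planned: 16 × 1,254 = 20,064 per country; × 4 = 80,256.
- Needed, per consenter: 16 × 376 = 6,016 per country; × 4 = 24,064.
- Difference: 14,048 per country; 56,192 in four countries.

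**Step 3: what 1,254 per arm delivers (per consenter).**

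- Power for 30% versus 40%: Φ[(0.10·√1254 − 1.3221)/√0.45] = Φ(3.31) = 99.95%. At 376 per arm the same formula gives Φ(0.92) = 82.1% (80% on the corrected formula).
- True difference detectable with 80% power: about 5.2-5.3 points upward.
- Observed difference that reaches p < 0.05: 1.96·√(2·0.3185·0.6815/1254) = 0.0365, that is, about 3.7 points. This is a different quantity from the one above.

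**Step 4: could multiplicity explain 1,254?** No. Bonferroni for 3 comparisons needs 475-495 per arm, and for 6 comparisons 550-570.

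**Step 5: the analysed denominator.** The protocol gives no refusal share, so it is assumed here: refusals are all non-consenters, in the same share in each arm. The ranges are uncorrected to corrected.

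| Assumed refusal share among those who engage | Contrast on CI/(CI+PI+R) | Engaged per arm | Consenters per arm | 1,254 divided by upper figure |
|---|---|---|---|---|
| 0% | 30% vs 40% | 356-376 | 356-376 | 3.3 |
| 25% | 22.5% vs 30% | about 540-565 | about 404-424 | 3.0 |
| 50% | 15% vs 20% | about 905-945 | about 453-473 | 2.7 |

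With 50% refusal, 376 consenters correspond to 752 engaged per arm. Power on the analysed rate is then Φ[(0.05·√752 − 1.0532)/√0.2875] = Φ(0.59), about 72%.

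**Step 6: totals as printed.** Column E: 334 + 3 × 3,762 + 5,016 + 2,508 + 1,254 + 3,376 = 23,774, not 23,773. Four countries: 1,336 + 80,256 + 13,504 = 95,096, not 95,092.

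**The case against.** The error is conservative. Power for the stated contrast is above 80%, and neither the type I error nor the estimates are harmed. The protocol also says that sizes will be updated with country-specific completion percentages. It plans outputs that gain from many completers: rates stratified by demographics, representativeness, and comparison of risk-factor prevalence with national estimates. And the factor of 3.3 compares respondents with known status against consenters, so it depends on the denominator.

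Most of this stands, but it does not remove the point. The update would use the same method and carry the error forward. The other outputs are never given as the reason for 376 completers, although they make keeping 1,254 a reasonable choice if it is justified openly. The dependence on the denominator is real, so the 3.3 must carry its condition. It falls to about 2.7 under an assumed 50% refusal. It would rise if the 30% and the 10 points were already meant on the analysed rate, because the 376 would then include refusers.

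A reader might also infer from Table 2 that each arm closes separately on reaching 376 completers, so that the better arm stops first and the slower one loses its concurrent comparison. The protocol does not say this. Its only run-until-complete rule is for the single-arm baseline survey, it sets 1,254 consents per arm, and it says that "A built-in randomization schema will randomly fork each dialed participant to one of the arms of the microtrial".

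**Conclusion.** The sample size statement for microtrials 1-6 is wrong as written. The 376 is a denominator, and treating it as completers uses the 30% twice. If the 30% and the 10 points are per consenter, enrolment is planned at 3.3 times what the stated power needs, and the design has 99.95% power for 10 points, or 80% power for about 5.2-5.3 points.

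Two stronger readings are not supported. A reader might infer that the trial is under-powered or its results invalid; the error goes the other way. A reader might also infer that 376 consenters per arm would be enough; that holds only if the contrast is defined per consenter, whereas the analysed rate counts refusals as well. Microtrial 7 is not affected by this point, because it is sized on the precision of kappa, for which completers are the right unit.

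The conclusion rests on a two-sided test, equal arms and an upward difference, all inferred from the exact match to 376. The refusal shares used in the check are assumptions.

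**What to change.** 1. In section III.B, describe 376 as respondents per arm with known completion status, and state that the test is two-sided, 30% versus 40%, with continuity correction.
2. Define the assumed 30% and the 10-point difference on the denominator of the analysed rate, CI/(CI+PI+R), with an explicit assumption for the refusal share.
3. Then choose one of two routes:
   - recompute Columns B to E of Table 1, the matching row of Table 2 and the totals on that denominator, without simply entering 376 as the number of consenters; or
   - keep 1,254, state that it gives 80% power for about 5.3 points per consenter, and give the reason for wanting that precision or that many completers.
4. Use the corrected method when the sizes are updated from the baseline survey.
5. If the other figures stay, correct the totals to 23,774 per country and 95,096 overall.

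The cost is protocol wording and tables. On the assumptions examined above, enrolment stays the same or falls.

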***4. Provide a brief data analysis* plan *and a description of variables to be derived.***

The contact rates, response rates, and completion rates will be tabulated for each of the microtrials by study arm; where contact, response, and completion rates are defined as:

The contact, response, and completion proportions^[[1]](#footnote-1)^ will be tabulated for each of the *microtrials* and by study arm where contact, response, and completion are defined as:

$$Contact Rate= \frac{CI+PI+R}{CI+PI+R+(NC+U)}$$

$$Response Rate= \frac{CI+PI}{CI+PI+R+NC}$$

$$Completion rate= \frac{\mathrm{CI}}{CI+PI+R}$$

**CI** (Complete Interview): a respondent that answered all applicable questions

**PI** (Partial interview): a respondent who consented to the survey but did not answer all questions

**R** (Refusal): a respondent who: 1) did not consent to the survey, or 2) formally withdrew during the survey

**NC** (Non-contact): a working phone number where the respondent picked up but did not engage with the survey. This is assessed by looking at the system log for time spent on the survey

**U** (Unknown): a phone number that cannot be determined whether it is a working phone number (the respondent did not pick up the phone) or not (the phone number is not eligible)

Respondents who report being less than 18 years old are considered ineligible. Ineligible respondents are excluded from the equations for contact, response, and completion rates.

Contact, response, and completion proportions will be compared by study arm for each microtrial and by incentive group. *A priori, a*n alpha of 0.05 will be used for hypothesis testing.

Partially completed surveys will be tabulated and stratified by both the question number, and the question content due to the randomization of NCD topic modules. Additionally, the average time spent answering, the number of “Don’t know” or “Refuse to answer” responses, and the number of times the question was repeated will be calculated for both the chronological question number and question content and stratified by study arm. For microtrial #7, test for agreement in survey responses between the survey modalities will be assessed using Cohen’s Kappa.

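### Microtrial 7's stated margin of error for kappa (0.05%, tied to 405 completers per arm) is wrong: the inputs give ±0.05 in kappa units for both arms pooled (810 pairs) and ±0.071 for one arm

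*Protocol*

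**What the plan says.** Protocol section III.B, under Microtrial 7, bases the size on precision: "This sample size is calculated based on the kappa statistic". The assumed value is 0.75, and the remaining inputs are printed together with the result: "margin of error of 0.05%, an alpha of 0.05, and the proportion of positive responses=0.3, 405 participants who have completed the survey per study" (that is, for each of two arms). The sentence does not say whether the margin refers to one arm or to both arms together.

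Table 1 multiplies 405 by two arms to give 810 completers per country. Table 2, in section V.C, repeats 405 per arm for microtrial 7 but prints a two-arm total of 752.

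The data analysis plan (section V.C.4) says that a "test for agreement in survey responses between the survey modalities will be assessed using" Cohen's kappa. It does not say whether kappa is estimated per arm or pooled. It contains no margin and no wrong figure.

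**The concern.** The margin of error is the only precision or power figure that justifies the size of microtrial 7, which is 3,376 consenting participants per country and 13,504 over four countries. It has two faults.

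- **Unit.** Kappa is not a percentage, and 0.05% read literally is 0.0005.
- **Basis.** The margin sits next to a per-arm count. A reader who silently drops the percent sign may then take ±0.05 to hold within each order arm (IVR first or CATI first).

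The precision is therefore overstated a hundredfold as printed. It is still overstated for a single arm once the unit is repaired.

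**Working it through.** **Inputs, all from section III.B:** kappa k = 0.75; proportion positive p = 0.3; alpha 0.05; 405 completers per arm; two arms.

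**Assumptions of this check:** a two-sided interval (z = 1.96, as sidedness is not stated), p equal in both modalities, and each of the 405 contributing one IVR–CATI pair.

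**Variance.** For a binary kappa with equal marginals,

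n × Var = (1 − k) × [(1 − k)(1 − 2k) + k(2 − k) / (2p(1 − p))]

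= 0.25 × [0.25 × (−0.5) + 0.9375 / 0.42]

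= 0.25 × [−0.125 + 2.2321] = 0.5268.

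The general Fleiss–Cohen–Everitt variance gives the same value.

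**Reproducing the plan's figure.** With n = z² × 0.5268 / d²:

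| Margin d | Pairs needed |
| --- | --- |
| 0.05 (kappa units) | 809.5, so 810 = 2 × 405 |
| 0.0005 (0.05% taken literally) | about 8.09 million |

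The match at d = 0.05 is exact once the arms are pooled. Other routes do not give 405 for one arm:

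- One-sided alpha needs 570 pairs for ±0.05.
- The simpler variance, observed agreement × (1 − observed agreement) / (1 − chance agreement)², needs 819.
- A margin of 5% of kappa (0.0375) needs 1,439.
- The variance under the null hypothesis needs about 2,122.

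**Precision delivered.** With d = 1.96 × √(0.5268 / n):

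| Pairs | Margin |
| --- | --- |
| 405 (one arm) | ±0.0707 |
| 810 (both arms) | ±0.0500 |
| 752 (Table 2's total) | ±0.052 |

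Simulation of the same 2 × 2 table (200,000 replicates) gives ±0.0708 at 405 pairs and ±0.0500 at 810. The one-arm margin is wider by a factor of 0.0707 / 0.0500 = 1.41, as expected from halving n.

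**Inflation to enrolment.** 405 / (0.30 × 0.80) = 1,687.5, so 1,688; × 2 = 3,376; × 4 = 13,504. These agree with the protocol.

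**Table 2.** 2 × 405 = 810, whereas 752 = 2 × 376, which is the total for a two-arm trial at 376 per arm (as in microtrial 5).

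**The case against.** The best defence is that the sample size itself is right. The inputs lead to 810, Table 1 prints 810, and an agreement kappa between modalities is naturally estimated from all pairs. If 810 are needed in two equal arms, then 405 per arm are indeed needed, so that clause is true on the pooled basis. What remains is a stray percent sign and a missing word. Most of this stands: the total is adequate and the pooled reading is the natural one. It does not rescue the sentence, because the printed margin is wrong on every reading and the basis that makes 405 correct is nowhere stated.

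Three stronger readings might be inferred, and the documents do not support them.

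- **The trial is undersized because each order arm reaches only ±0.071.** The protocol sets no precision target by order, and the analysis plan names no by-order kappa. The description of microtrial 7 in section V.C speaks of response consistency adjusted for priming. Adjustment can use all 810 pairs and does not require a separate kappa for each order.
- **The plan needs 8.1 million pairs.** A margin of 0.0005 is plainly not intended. That figure only shows that the unit is an error.
- **The single planning prevalence of 30% is a mistake.** It is openly stated as an assumption, and the protocol gives no expected item prevalences that contradict it. Margins for rarer items are useful context, not a correction.

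**Conclusion.** The point holds as an error in stated precision. The margin should read ±0.05 in kappa units, not 0.05%, and it applies to 810 pairs pooled over both arms. One arm of 405 gives ±0.071, about 41% wider. Enrolment is adequate for a pooled kappa, and the inflation arithmetic is correct.

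This rests on kappa 0.75, 30% positive in both modalities, two-sided 95% confidence and the large-sample variance. Under one-sided alpha, 405 pairs would still give only ±0.059. Table 2's total of 752 contradicts both its own 405 per arm and Table 1's 810.

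**What to change.** In section III.B, restate the precision along these lines: *margin of error ±0.05 in kappa units for the estimate pooled over both arms (810 pairs, 405 per arm) at 30% positive responses; about ±0.07 for any kappa reported within one order.*

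In Table 2, change the two-arm total for microtrial 7 from 752 to 810.

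Optionally, add that the pooled margin widens for rarer items. If kappa stays at 0.75, the same formula with 810 pairs gives:

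- at 10% positive, n × Var = 0.25 × [−0.125 + 0.9375 / 0.18] = 1.2708, so about ±0.08 (0.078);
- at 5% positive, n × Var = 0.25 × [−0.125 + 0.9375 / 0.095] = 2.4359, so about ±0.11 (0.107).

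The cost is one sentence and one table cell. No enrolment figure or planned analysis changes, but the stated precision becomes less favourable than the one printed.

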**IV. Participants**

***Describe the study participants and the population from which they will be drawn. Specify the inclusion and exclusion criteria. If you plan to include children, note their ages and whether you will include children in foster care. Note if the participants are particularly vulnerable in terms of cognitive limitations, education, legal migration status, incarceration, poverty, or some combination of factors.***

The protocol’s activities will be conducted in four of the following countries: Bangladesh, Lebanon, Kenya, Uganda, Tanzania, and Ghana. The PI and Co-I’s are actively engaging academic and research institutes from each of these six countries in order to secure their partnership.

Objectives 1,2 and 4

For *microtrials #1-5* from Objectives 1 and 2 and *microtrial #7* from Objective 4, potential participants will be randomly selected to answer an IVR survey (or CATI for *microtrial #7)*  through random digit dialing (RDD). Using the mobile network operator identifying digit sequence as the base (e.g.all of MNO X’s phone numbers start with either 072, 077, or 079) the remaining digits will be randomly generated to create a random sample of mobile phone numbers to which IVR surveys will be delivered. Numbers will then be dialed by computer software, connected to phone lines, until a human respondent answers the call.

Upon connecting to an active line, participants will be asked to select the language in which they would like to answer the survey. After hearing a brief introduction, participants will be asked to enter their age. Participants will be excluded from the survey if they report being less than 18 years old. There are no other inclusion or exclusion criteria for *microtrials* #1-5.

Objective 3

*Microtrial* #6 relies on phone numbers provided by an MNO or from a household survey where participants have consented to release their phone number for other studies. Participants in *microtrial* #6 will answer the same questionnaire as participants in *microtrials* # 1-5 and will similarly be screened for exclusion based on age---where those who report being less than 18 years old will be excluded.

